## **6) STUDY PARTICIPANTS**

The local research midwives and nurses will be trained to discuss specific aspects of this study, to obtain informed consent and apply the electrodes and blood pressure cuff for the MONICA AN24 device and the NICOM system. The local Principal Investigator, Chief Investigator and co-investigator can be contacted if there are any concerns regarding adherence to the protocol and to deal with any issues arising from the investigations.

### **6.1 Inclusion Criteria: (IRAS A17-1)**

- Viable singleton pregnancy  $\geq 28$  weeks' gestation
- No fetal anomalies according to Fetal Anomaly Screening Programme definition
- Ability to give written informed consent
- Maternal Age >16 years

### **6.2 Exclusion Criteria: (IRAS A17-2)**

- Unable to read English (as the survey instruments are only available in English)
- Multiple pregnancy
- Pre-existing maternal cardiovascular or respiratory disease
- Fetal anomaly
- Contraindication to lying prone (severe pain etc.)
- Allergy to self-adhesive electrodes used for standard electrocardiography (ECG)
- Unable to give written informed consent

### **6.3 Recruitment:** (IRAS A27-1 – A35)

We will conduct a cohort study of women with a viable singleton pregnancy over 28 weeks' gestation. Women at low-risk of complications will initially be approached in routine antenatal clinics from 20 weeks' gestation, women who agree to hear more about the study will then be given brief information about the study and will then be asked to complete a consent to contact form to allow the researchers to contact them at an appropriate point in their pregnancy. If women are willing to participate in the study when they are contacted, they will be sent a participant information sheet. Written consent will be taken prior to participating in the study.

### **6.5 Participants who withdraw consent [or lose capacity to consent]:**

Participants can withdraw consent at any time without giving any reason, as participation in the research is voluntary, without their care or legal rights being affected. For participants who voluntarily withdraw from the study who have previously consented to the study data up to the time of withdrawal will be included in the study unless the participants specifically request for all of their data be removed.

As participation in the study is limited to a single window during which participants will have a period of monitoring capacity to consent will be continuously monitored. After this period of contact ongoing capacity will not be assessed and participants' data will be included in the study unless participants specifically request for their data to be removed.

## **7) OUTCOME MEASURES** (IRAS A57, A58)

The study is anticipated to last for six months (at a recruitment rate of two participants per week) and will commence in January 2020. It is estimated that data cleaning and analysis will take an additional three months.

### **Primary Outcome Measure**

Maternal cardiac output as assessed by non-invasive cardiac monitoring.

### **Secondary Outcome Measures**

A variety of other measures of maternal cardio-respiratory status will be measured, including: heart rate, blood pressure, respiratory rate and oxygenation via pulse oximetry.

Fetal wellbeing assessed by continuous cardiotocography which will report baseline heart rate, variability, the presence of accelerations or decelerations.

Acceptability, including maternal anxiety, will be assessed using standardised measures and comfort using a user-completed questionnaire.

## **8) DATA COLLECTION, SOURCE DATA AND CONFIDENTIALITY (IRAS A36-A45)**

The study will be carried out at single tertiary maternity unit (St Mary's Hospital, Manchester). [name] will be the Chief Investigator and the Principal Investigator at the St Mary's site. The day-to-day running of the project will be carried out by the local research midwife or nurse from the participating unit. Any problems or queries will be passed to the Principal Investigator in the first instance. In their absence the Chief investigator will deputise.

Data will be initially collected on written case report forms by the local research midwives/nurses who will then input the information onto a secure database (in RedCap). All records will be double entered to check for validity. The case report forms will be stored as the original study record in a dedicated file.

All study data will be entered into a database customised for the study in which the participant will be identified only by a specific study number. The participants name and other identifiable data will be stored in a separate database linked only by the study number. All data generated by the study will be preserved and stored with no patient identifiable details for 5 years after completion of the study. [name] will be custodian of the data on behalf of the Sponsor. Electronic data will be stored in appropriate data storage devices. All electronic and hard-copy data files will be stored securely in accordance with local policy. Storage of electronic data will be on password protected files on a restricted area of a file server which is in a secure location. Data will be processed on a workstation by authorised staff using passwords.

## **9) STATISTICAL CONSIDERATIONS**

### **9.1 Statistical Analysis (IRAS A56, A62)**

Data regarding maternal characteristics will be analysed using descriptive statistics. Data regarding maternal cardiac output in different maternal positions will initially be evaluated to determine whether values are normally distributed. Depending on the distribution of values, they will be transformed to a normal distribution if appropriate and a repeated measures ANOVA performed. If they are not normally distributed and transformation does not achieve a normal distribution a Friedman test will be performed. This approach will address variation between individual participants.

Descriptive and comparative statistical analysis will be conducted in STATA (STATACORP, TX, USA). As the investigators anticipate some variation in the baseline observations between participants both raw values and change from baseline status will be evaluated.

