##### **5.2 Study Intervention and/or Procedures (IRAS A13, A18, A19)**

Prior to commencing the study women will be asked to complete a short questionnaire about their pregnancy which will ask about symptoms of pain or discomfort, their anxiety levels and prior knowledge and experience of maternal position during sleep or rest. They will then have fetal and maternal monitoring connected via a series of self-adhesive electrodes. The fetal heart rate and uterine activity will be monitored using the MONICA AN24 system which has been used previously by our group to monitor fetal heart rates for extended periods [11]. This involves application of five self-adhesive ECG electrodes to the maternal abdomen (Figure 2).

[figure not shown]

Figure 2 – MONICA AN24 fetal monitoring system showing electrodes applied to

Maternal cardiac output, heart rate and blood pressure will be measured by the Cheetah NICOM system which has self-adhesive electrodes applied to the maternal back and a blood pressure cuff to the maternal upper arm. The NICOM system has previously been validated for use in pregnancy [12]. A pulse oximetry probe will be applied to the left forefinger. The mother will be asked to lie

on her left-hand side (the optimal position for maternal and fetal wellbeing) for 20 minutes with observations recorded at 5-minute intervals on to a case report form.

If any of the maternal or fetal values are outside of the anticipated range the experimental protocol will be discontinued. Women who have hypertension (>140/90 mmHg), tachycardia (>110 bpm), tachpnoea (>20 breaths per minute) or abnormal fetal heart rate traces will be referred to the maternity service for further assessment. A transfer letter template has been devised to rapidly report problems to the receiving medical team.

If the maternal and fetal observations are normal during the period spent in left lateral position the mother will be positioned in the prone position on the device for a period of 30 minutes. During this time observations recorded at 5-minute intervals on to a case report form. If at any point the mother feels unwell or the observations become abnormal (as outlined above) the experimental protocol will be ceased and the mother returned to a left lateral position. If there are persistent abnormalities of the fetal heart rate trace the mother will be referred urgently to the maternity service.

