## **9.2 Sample Size: (IRAS A59, A60)**

The sample size for this study has been calculated to determine whether maternal cardiac output (the primary outcome measure) decreases in the prone position compared to left lateral position. Milsom et al. demonstrated a mean cardiac output of 6.6L/min in left lateral position, 5.9L/min in right lateral position and 5.5L/min in a supine position and there was a standard deviation of 1.0L/min [1]. To have 80% power to detect a fall from the level reported for left lateral position (6.6 L/min) to 5.7 L/min (the midpoint between right lateral and supine positions) 20 participants would be required in each group using  $\alpha=0.05$ .

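### Section 9.1 chooses the primary test by checking the raw cardiac output values for normality, but the repeated measures ANOVA relies on within-woman residuals or differences (minor: small power cost, but the scale of the primary result can change for an irrelevant reason)

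*Protocol*

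**What the plan says.** The primary outcome is cardiac output (section 7: "Maternal cardiac output as assessed by non-invasive cardiac monitoring"). Each woman is her own control: section 5.2 has 20 minutes left lateral, 30 minutes prone and 20 minutes left lateral again, with readings every 5 minutes.

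Section 9.1 gives the rule for the primary test in three steps:

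- Check: cardiac output in the different positions "will initially be evaluated to determine whether values are normally distributed".
- Parametric branch: depending on the distribution, "they will be transformed to a normal distribution if appropriate and a repeated measures ANOVA performed".
- Rank branch: "If they are not normally distributed and transformation does not achieve a normal distribution a Friedman test will be performed".

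The section adds that, because baseline observations are expected to vary between participants, "both raw values and change from baseline status will be evaluated". That sentence is not linked to the normality check or to the choice of test.

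Section 9.2 states the question that the study is sized for: "whether maternal cardiac output (the primary outcome measure) decreases in the prone position compared to left lateral position". The sizing is in L/min, a fall from 6.6 to 5.7 with SD 1.0.

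**The concern.** The rule checks the wrong quantity. The distribution of raw values across women mixes two things: how women differ from each other, and how a woman's readings vary around her own level. The first usually dominates when the within-woman correlation is high. It cancels in the comparison of positions, and only the second matters for the ANOVA.

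A skewed or two-peaked spread of women's usual cardiac output can therefore move the primary analysis to another scale although nothing is wrong with the ANOVA. At stake is what the primary result means. Under the three branches it is a mean change in L/min, a change on a transformed scale, or a statement about ranks. Only the first can be set directly against the 0.9 L/min fall in section 9.2. There is also some loss of power when Friedman replaces a valid ANOVA.

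**Working it through.** **1. The plan's own figure.** Inputs from section 9.2: fall 6.6 − 5.7 = 0.9 L/min, SD 1.0 L/min, power 80%, α = 0.05 (sidedness not stated).

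n per group = 2 × (1.960 + 0.842)² × 1.0² / 0.9² = 2 × 7.85 / 0.81 = 19.4, so 20.

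The stated 20 reproduces with the two-sided formula for two independent groups. That formula contains no within-woman SD or correlation, and the protocol gives neither. The within-woman correlation ρ below is therefore an assumption, shown as a range.

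**2. Why raw values are the wrong object.** Write the value for woman i in period j as y = μ + aᵢ + pⱼ + eᵢⱼ, where aᵢ is her own level, with total variance 1.0² and ρ = var(a)/1.0².

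- Raw value in one position: variance var(a) + var(e). A share ρ of it comes from aᵢ.
- Prone minus left lateral: (p_prone − p_left) + (e_prone − e_left). The term aᵢ is gone.

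If e is normal, the differences are exactly normal whatever the shape of a, while the raw values have skewness ρ^1.5 × skewness(a). A lognormal with shape s has skewness (e^(s²) + 2)√(e^(s²) − 1):

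- s = 0.8 gives (1.896 + 2) × √0.896 = 3.7. With ρ = 0.8 the raw skewness is 0.716 × 3.7 = 2.6, and that of the differences is 0.
- A lognormal with the protocol's mean 6.6 and SD 1.0 has s = √ln(1 + 1/6.6²) = 0.15 and skewness (1.023 + 2) × √0.023 = 0.46. This is the mild case.

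**3. How often the rule switches.** Simulation of the whole rule with 20 women, three periods, total SD 1.0 and normal within-woman errors, so the ANOVA is valid. Assumed, because the protocol does not say: Shapiro-Wilk at 0.05 in each position, log as the transformation, then Friedman if any position still fails.

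| Between-woman levels | ρ | Friedman reached |
|---|---|---|
| Normal or mildly skewed (s about 0.15) | 0.3 to 0.8 | about 7-10% |
| Strongly skewed (s = 0.5 to 0.8) | 0.8 | about 25-44% |

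Part of the 7-10% comes simply from testing three positions at 5% each. A separate simulation with its own skewed shape gave about 20%, 34% and 62% at ρ = 0.5, 0.7 and 0.9, so the rate keeps rising with ρ.

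**4. What a switch costs.** Power at the planned 0.9 L/min fall with three periods, always ANOVA against always Friedman:

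| ρ | ANOVA | Friedman |
|---|---|---|
| 0 | 82% | 68% |
| 0.3 | 93% | 83% |
| 0.5 | 98% | 94% |
| 0.7 | 100% | 99% |
| 0.9 | about 100% | about 100% |

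At 0.5 L/min and ρ = 0.5 the comparison is about 59% against 47%.

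**5. Net cost of following the rule.** Roughly, net loss = chance of a switch × loss given a switch. At 0.9 L/min and ρ = 0.3, with normal or mildly skewed levels: 0.10 × (93 − 83) = 1.0 point. At ρ = 0.5 with skewed levels: 0.20 × (98 − 94) = 0.8 point. At 0.5 L/min and ρ = 0.5: 0.20 × (59 − 47) = 2.4 points.

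Simulating the whole rule gives at most about 1.5 points at 0.9 L/min and up to about 4 points at 0.5 L/min (for example 82.7% to 78.9% with the most skewed levels). The separate simulation gave 59% to 56% (ρ = 0.5) and 83% to 77% (ρ = 0.7) at 0.5 L/min. Type I error stayed at about 3-6% throughout.

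**The case against.** The best case against acting is that little is lost. Switches are most frequent at high ρ, where both tests have nearly full power for a 0.9 L/min fall. With normal or mildly skewed levels the switch is uncommon, and recruiting low-risk women without cardiovascular or respiratory disease gives no reason to expect extreme skew. Section 9.1 also promises change from baseline, so within-woman changes will be examined whichever test is used. The primary objective in section 4.1 is to describe, and how an assumption is checked is often left to an analysis plan. All of this stands as to size, and it makes the point minor.

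It does not remove the point. The protocol does not leave the rule open: it names the values as the object of the check and makes the primary test depend on the answer. The sentence on change from baseline is not tied to that choice.

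A reader might infer more, and the documents do not support it:

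- **That pooling all 5-minute readings makes the check fail through clustering.** Section 9.1 speaks of values in different positions, which points to a check by position, and pooling is nowhere stated.
- **That Friedman collapses to a sign test.** That needs only two positions. Section 5.2 defines three periods.
- **That the check would hide a minority of women with a large fall.** How well a check on differences would reveal this depends on a within-woman SD that the protocol does not give. Section 5.2 also stops the procedure for a woman whose observations become abnormal, and section 11 reports such terminations.

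**Conclusion.** The point holds as a minor one. As written, section 9.1 lets variation between women, which is unrelated to position, decide whether the primary result is a mean change in L/min, a change on a transformed scale, or a rank test. The harm is mainly to interpretation against the L/min sizing in section 9.2.

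The documents do not support reading this as a serious loss of power or a threat to type I error. Over the main range of ρ (0.3 to 0.8), the net loss is about 1.5 points or less at the planned fall and about 4 points at 0.5 L/min. One alternative set of assumptions gave 6 points at 0.5 L/min. The loss given a switch is larger, but a switch is frequent only with strong skew and high correlation.

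These sizes rest on an assumed ρ, Shapiro-Wilk at 0.05 by position, a log transform, and normal within-woman errors with equal correlation between periods. The argument about which quantity to check rests on none of the numerical choices.

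**What to change.** In section 9.1:

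- Replace the check on raw values by a check of the repeated measures model residuals, or of the within-woman prone-minus-left-lateral differences, for example by Q-Q plot.
- Make the repeated measures analysis of cardiac output in L/min the primary analysis whatever the distribution of the raw values. Report the mean within-woman difference with its 95% CI.
- If the differences are clearly non-normal, add as a sensitivity analysis a signed-rank test with the Hodges-Lehmann estimate and interval, or a bootstrap interval, on the same L/min differences. This takes the place of the switch to Friedman.

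The cost is a few sentences in section 9.1. It needs no extra participants or measurements, and the planned 20 is unchanged. The small downside is giving up the data-driven choice of primary test.

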#### **4) STUDY OBJECTIVES**

##### **4.1 Primary Question/Objective: (IRAS A10)**

To describe the cardiorespiratory effects for a mother maintaining a prone position supported by the cushion (Anna cushion) for a period of 30 minutes.

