Following a 30-minute period in the prone position participants will then be returned to the left lateral position for 20 minutes of further monitoring with observations recorded at 5-minute intervals. After this period the monitoring will be disconnected and the electrodes removed. The site will be checked for signs of skin irritation. Women will then be asked to complete a short questionnaire to describe their experience of using the device and a final survey of their anxiety levels. Women will then be given a small token of thanks for their participation.

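### The Friedman fallback for cardiac output suits the prone versus left-lateral contrast poorly and carries no interval in L/min; a paired rank analysis would fit better (low severity)

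*Protocol*

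**What the plan says.** The primary outcome is "Maternal cardiac output as assessed by non-invasive cardiac monitoring" (Protocol, Primary Outcome Measure), and the primary objective in section 4.1 is "To describe the cardiorespiratory effects for a mother maintaining a prone position". Section 9.1 begins with a distribution check: "Data regarding maternal cardiac output in different maternal positions will initially be evaluated to determine whether values are normally distributed". A repeated measures ANOVA follows, after transformation where appropriate. Otherwise: "If they are not normally distributed and transformation does not achieve a normal distribution a Friedman test will be performed". The same section says separately that the values themselves and the changes from baseline will both be looked at, and ties this to neither test.

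Section 5.2 describes three consecutive periods in two positions:
- left lateral, "for 20 minutes with observations recorded at 5-minute intervals";
- then "positioned in the prone position on the device for a period of 30 minutes";
- then "returned to the left lateral position for 20 minutes of further monitoring".

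Section 9.2 sizes the study to learn whether cardiac output "decreases in the prone position compared to left lateral position". Section 9.1 does not say whether the repeated conditions are the two positions, the three periods or the individual 5-minute readings.

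**The concern.** The sizing question is a single paired contrast, with a direction and a size in L/min. Friedman ranks each woman's values among themselves, so it answers something else under either natural reduction of the data:
- With two conditions it keeps only the direction of each woman's change.
- With three it tests whether any period differs from any other, so a shift confined to the recovery period can produce a significant result.

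The statistic also brings no estimate or interval to set beside the 0.9 L/min planning difference. If the fallback were triggered, a real fall could be harder to detect, and a significant result could be harder to attribute to the prone position.

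The trigger adds to this. The check in 9.1 is on the values, not on the within-woman differences. Unusual variation between women could therefore set off the fallback while the differences are close to normal, which is where Friedman gives up most against a paired analysis.

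**Working it through.** **1. The plan's own figure.** From section 9.2: fall 6.6 − 5.7 = 0.9 L/min, SD 1.0, α = 0.05, power 80%. The two-sided, two-group formula gives n = 2(1.960 + 0.842)² × 1.0² / 0.9² = 19.4, so 20 per group, with 81.2% power at 20. The stated 20 is reproduced. One-sided it would be 16. This is a formula for independent groups, and the protocol gives no within-woman SD or correlation, so those are assumed below.

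**2. Two conditions.** Suppose cardiac output is lower prone in p of n women. The rank sums are n + p and 2n − p, and

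Q = [12/(n·2·3)]·[(n + p)² + (2n − p)²] − 9n = (2p − n)²/n,

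which is the squared sign-test statistic. For n = 20 and p = 13, Q = 36/20 = 1.8 by either route.

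**3. Relative efficiency under normality.** For Friedman against ANOVA this is (3/π)·k/(k + 1), where k is the number of conditions:
- k = 2: 0.637
- k = 3: 0.716
- k = 14: 0.891, taking 20/5 + 30/5 + 20/5 = 4 + 6 + 4 readings

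For the signed-rank test on within-woman differences it is 3/π = 0.955. The value for k = 14 needs exchangeable readings within a woman. With no effect and serially correlated readings (assumed AR(1)), the simulated level was 6.5% at correlation 0.5 and 9.9% at 0.8.

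**4. Three periods and the contrast.** With prone equal to the first left-lateral period, a 0.5 L/min shift in the last period only, n = 20 and assumed noise SD 0.6, three-period Friedman rejected in 61% of simulated trials.

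**5. Power at the planned fall.** Inputs: n = 20, fall 0.9 L/min, assumed independent period-level SD 1.0. The signed-rank test uses prone minus the average of the two left-lateral periods (SD of the difference √(1 + ½) = 1.22 L/min).

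| Noise | Friedman, three periods | Signed-rank, averaged |
|---|---|---|
| Normal | 0.68 | 0.86 |
| Laplace | 0.81 | 0.89 |
| t, 4 df | 0.82 | 0.90 |
| Lognormal (log-scale SD 1) | 0.98 | 0.96 |

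Both tests cancel each woman's own level, so the normal row also applies when women's levels are oddly distributed but the within-woman noise is normal.

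**6. First left-lateral period only.** The SD of the difference is now √2 = 1.41 L/min.

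| Noise | Friedman, two values | Signed-rank, first period | Friedman, three periods |
|---|---|---|---|
| Normal | 0.56 | 0.73 | 0.68 |
| Laplace | 0.70 | 0.80 | 0.82 |
| t, 3 df | 0.81 | 0.88 | 0.91 |
| Lognormal (log-scale SD 0.8) | 0.90 | 0.90 | 0.95 |

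**7. Smaller noise.** With assumed SD 0.6 and the same 0.9 L/min fall, three-period Friedman and the averaged signed-rank test both exceed 0.96 for every shape tried (normal: 0.985 against 0.997).

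**8. Level of the replacement.** With both left-lateral periods averaged and strong skew, the signed-rank level rises to about 7%, against about 5% for three-period Friedman. With the first period alone it stays near 5%.

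**The case against.** Friedman is the usual rank counterpart of repeated measures ANOVA, and the number of conditions is a detail that a statistical analysis plan often supplies. Three stronger readings are tempting, and the protocol supports none of them.

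- *The fallback is a sign test.* A reader might infer this from the two positions. But there are three periods and about 14 readings, and 9.1 does not say how they are reduced. It is a sign test only with one value per position.
- *The fallback costs about a third of the efficiency.* That is 1 − 0.637 for two conditions under normality, whereas the fallback applies when the values have failed a normality check. Sign-test efficiency against the t test is 0.96 for differences following t with 5 df, 1.62 for t with 3 df and 2.0 for Laplace, but 0.33 for uniform. The loss can vanish, reverse or grow.
- *The effect estimate is lost.* Section 9.1 evaluates values and changes from baseline whichever test is run, so a change in L/min will be available. What is missing is an estimate with an interval tied to the fallback.

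The replacement also has a weakness: signed-rank and sign-flip tests rely on symmetric differences, and persistent skew is a plausible reason for the fallback to be used at all.

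All of this stands and limits the point. It does not remove it. The protocol itself names the test, so an analysis plan that followed it would inherit the mismatch with section 9.2. And because the check is on values rather than differences, a triggered fallback does not mean that the differences are non-normal.

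**Conclusion.** The point holds in a conditional form and is of low severity. If the fallback is used, Friedman is either a sign test (one value per position) or an omnibus test that does not isolate prone versus left lateral (three periods), and neither supplies an interval in L/min. At the planned 0.9 L/min fall with an assumed independent SD of 1.0, an averaged signed-rank analysis gains 18 points of power with normal noise and 8 with Laplace or t (4 df) noise, and loses 2 under strong lognormal skew. At an assumed SD of 0.6 the difference is negligible. The size therefore rests on a within-woman SD that the protocol does not give, on the shape of the data, and on whether both left-lateral periods are used. The case for change rests as much on matching the test to the stated contrast and reporting an interval as on power.

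**What to change.** Replace the fallback sentence in section 9.1. If the fallback is triggered, form each woman's prone-minus-left-lateral difference in cardiac output, stating in advance whether the left-lateral value is the first period or the average of both. Test the difference by Wilcoxon signed-rank or a sign-flip permutation test, and report the Hodges-Lehmann estimate with its 95% confidence interval in L/min.

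This costs a sentence or two and needs no new data. The choice of left-lateral value is a trade-off. Averaging both periods gives more power, but under strong skew the level rises to about 7% with no power gain. Using the first period alone keeps the level near 5% but gives up some power, with little or no advantage over three-period Friedman for heavy-tailed data. If Friedman is kept instead, 9.1 should state the number of conditions and name the paired estimate and interval to be reported with it.
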